Burn injuries affect not only the individual but also their family and community. Burn survivors experience long-term physical, psychological and social consequences (8, 10, 11). Longitudinal and experimental studies indicate that preexisting mental health conditions in both burn survivors and caregivers are closely related to survivors’ rehabilitation and psychological outcomes (12, 13). Many burn patients experience functional limitations shortly after the burn incident, limiting their ability to return to work or daily activities (11, 14). Burn incidents also affect patients’ families. Both patients and family members are at risk of developing post-traumatic stress disorder (PTSD) and experiencing guilt, stigma and discrimination, thus adversely affecting their quality of life (8, 11, 14). In countries where physical appearance is highly valued, burn survivors are often subject to harassment and negative, judgmental words (15). They experience increased distress in response to burn scars and other physical changes, leading to lower negative body image, self-esteem and social isolation (15).

There have been significant advancements in clinical burn care, the successful implementation of preventative initiatives and increased public awareness in high-income countries (16, 17). These advancements have led to a significant decrease in burn injuries and an increase in appropriate, high-quality care (16). Nonetheless, many LMICs still lack effective preventive measures, leading to persistently high rates of burn injuries (18–20). These injuries often occur without access to even the most fundamental health care, which can lead to avoidable fatalities, disabilities and social stigmatisation (18–20). In Pakistan, despite a population of more than 225 million and a high estimated incidence of burn injuries, insurance coverage and rehabilitative services are limited; this includes inadequate initial management of burn wounds and insufficient mental health care, leading to high rates of post-burn complications, such as contractures, PTSD and Common Mental Disorders such as anxiety and depression (21). Additionally, there is a lack of awareness of burn incidents and the challenges that burn survivors and their caregivers endure (21, 22).

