### Research design

2.1

This study is a cohort study with three measurement points conducted at 6- to 12-month intervals (*n* = 600). The impact of the health communication campaign will be evaluated by measuring indicators of knowledge, attitudes and practices related to burn first aid, as well as psychological variables and health information-seeking variables, among the following groups: the exposure group (i.e., burn survivors [*n* = 200] and caregivers [*n* = 100] exposed to campaign messages), the non-exposure group (i.e., burn survivors [*n* = 250] not exposed to campaign messages) and the Photovoice group (i.e., burn survivors [*n* = 50] who participate in Photovoice and are exposed to the campaign messages). Figure 1 presents the campaign process and the planned activities in different phases.

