#### Sampling

2.2.1

A combination of snowball and purposive sampling methods will be used to identify and recruit patients (burn survivors), caregivers and key stakeholders (i.e., health and emergency care professionals and key informants, including community leaders and policymakers), based on the eligibility criteria described below.

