##### Burn survivors

2.2.4.1

The following are the inclusion criteria for burn survivors:

Adults aged 18 years and aboveRecent (i.e., within the past 3 months) and/or past experience of a burn injuryResides in one of the seven research sitesAble to provide consent and participate in the mixed methods study, which requires their engagement in project activities, including surveys, Photovoice reflection workshops and closed/open exhibitions depending on the group to which they are assignedFor those involved in the Photovoice group, an additional criterion includes willingness to engage with participatory creative methods, such as photography and storytelling, as well as availability to attend a minimum number of Photovoice workshops.

The following are the exclusion criteria:

Burn survivors with intentional and/or self-inflicted injuries will be signposted to the available services for further help and will not be included in the study.

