##### Sampling

2.3.1.1

To investigate the preliminary effects of Photovoice on the primary and secondary outcomes of interest, we will categorise participants into three groups, as described previously (see Figure 1). As this is only a pilot study and the objective is mostly to co-adapt the Photovoice programme and evaluate its potential in building capacity for a larger evaluation, no sample size calculation has been deemed appropriate (48, 49). This study will also help us determine whether we can maintain an acceptable attrition rate of Photovoice for a future RCT (50). An effective sample size for this study was determined based on the sample size of previous exploratory studies using Photovoice (31).

Consenting baseline participants will be invited to attend the introductory Photovoice workshop via email and/or a telephone call. The invitation letters will be sent via email and/or postal mail. One-to-one meetings will be organised with those who do not want to be in a group setting.

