## Data analysis plan

4

To compare changes in self-reported outcomes within groups across two time points (see Table 1) in the sample (*N* = 600), we will implement linear mixed-effects models implemented in R (R version 3.6.1) (51) using the lme4 package and in SAS 9.4. This method considers correlations within participants, allowing them to be modelled appropriately. It also estimates within-subject variability, in addition to estimating model parameters. The method can handle and model missing outcome data under the assumption that the data are missing at random. The mixed model uses a longitudinal data structure that includes both fixed and random effects, and baseline measurement is usually included as a covariate. Time will be included in the model as an interacting categorical variable to observe any time-varying trends. Cohen’s *d* for the effect of Photovoice will be calculated as the difference between baseline-corrected estimated means divided by the pooled standard deviation. A two-sided *p* < 0.05 indicates statistical significance. In addition, demographic variables, such as age, education, gender, marital status, geographic location (i.e., rural vs. urban residence) and household situation (i.e., living with a single and/or an extended family) will be included in the linear mixed models to test for potential moderating and mediating effects on behavioural intention related to burn prevention and first-aid practices. A stepwise selection of the variables will be conducted to determine which variables to keep in the model. As we add the variables, we will immediately eliminate those that do not reduce the Akaike information criterion (AIC) by using the *stepAIC* R function from the library *MASS*. If two or more independent variables in a model are found to be strongly correlated, a variance inflation estimate of less than 5 will be used to determine whether collinearity is present. If the relationship is found to be non-linear, attempts will be made to model the outcome data via the use of splines or polynomials in the *nlme* package in R. The normality of residuals will be assessed graphically using histograms and Q-Q plots. Detailed statistical analyses following Good Clinical Practice: Consolidated Guidelines ICH E9 (52) and Medical Research Council guidelines for developing complex interventions (53) will be described in the statistical analysis plan, which will be finalised before the data lock stage.

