In line with the flexibility of the Photovoice approach as a participatory action research method, we decided to follow reflexive thematic analysis based on Braun and Clarke’s six-phase approach (54), with NVivo software supporting data management and coding. All reflection sessions and exhibitions will be audio-recorded, transcribed verbatim and pseudonymised. Two researchers will independently code a subset of transcripts to enhance rigour and then collaboratively develop an analytical framework. Both inductive and deductive coding will identify emergent themes. Thematic analysis will be conducted on captions, participant narratives and social media comments. Special attention will be given to potential group differences (e.g., male vs. female participants, urban vs. rural residence, severity of burn injuries, and communication or health literacy differences). Data analysis will occur in parallel with data collection. Thick descriptions of the context of each workshop and the interactions with each participant will be documented in field notes. The team will agree when data saturation has been reached.

Social media metrics and textual analysis of photo captions and viewer comments will be employed to determine audience reach and engagement. These metrics will also provide insights into perceptions, knowledge and attitudes related to burn survivors and their experiences. The analytics dashboards provided by each social platform will be used to gather key metrics. The main metrics include likes, comments, shares and emojis. Specifically, the comments will be used for thematic analysis to extract more narratives, stories and lived experiences. Overall, a triangulation approach will be used to integrate the results from the different data sources, provide a comprehensive overview of the findings and enhance confidence in the conclusions (55).

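### Recent and older burns are mixed across groups not described as randomised, and the model names no time-since-burn term, so recovery could pass for, or hide, a campaign or Photovoice effect

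*Protocol article*

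**What the plan says.** **Who enters.** Section 2.2.4.1 (Burn survivors) accepts adults whose burn occurred within the past 3 months, or earlier, or both. It sets no upper limit on time since injury.

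**How groups arise.** Section 2.1 states: "This study is a cohort study with three measurement points conducted at 6- to 12-month intervals". Section 2.2.1 adds: "A combination of snowball and purposive sampling methods will be used to identify and recruit patients (burn survivors), caregivers and key stakeholders". For group formation, section 2.3.1.1 says only that "we will categorise participants into three groups, as described previously". For Photovoice members, "an additional criterion includes willingness to engage with participatory creative methods, such as photography and storytelling", together with availability for workshops. No randomisation, matching or stratification is described. The exposure group is "burn survivors [*n* = 200] and caregivers [*n* = 100] exposed to campaign messages", the non-exposure group has 250 survivors and the Photovoice group has 50.

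**What the model contains.** Section 4 describes linear mixed models with the baseline measurement usually included as a covariate and time as an interacting categorical variable. The further variables named are "demographic variables, such as age, education, gender, marital status, geographic location (i.e., rural vs. urban residence) and household situation". Their stated purpose is to test moderation and mediation of behavioural intention, and stepwise AIC decides which remain. Time since burn is not mentioned. Injury severity appears only in the thematic analysis, where "severity of burn injuries" is one of the group differences to be examined. Further statistical detail is left to a separate analysis plan, to be completed before the data are locked.

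**The concern.** The protocol draws a line between recent and past burns at entry and then makes no stated use of it in the quantitative analysis. Groups formed by purposive and snowball recruitment, and in the Photovoice group also by willingness and availability, can differ in how recently their members were burned. The Introduction gives one reason to expect this: "Many burn patients experience functional limitations shortly after the burn incident". People still limited in daily activity may be less able to attend workshops.

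Scores such as resilience, self-stigma, social interaction anxiety and life satisfaction could plausibly change faster in the first year or two after injury than later. If so, the group with more recent burns changes more whatever the campaign does, and the non-exposure group no longer shows what would have happened without it. Depending on the direction of the imbalance, the campaign or Photovoice effect is overstated or hidden. The baseline score captures where a person starts, not how fast that person is changing.

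**Working it through.** There is no figure in the plan to reproduce on this point. The check asks whether baseline adjustment alone removes the bias.

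**Inputs from the protocol article:** 200 exposed, 250 non-exposed and 50 Photovoice survivors (section 2.1); baseline score as covariate and two-sided 5% level (section 4).

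**Assumed inputs (the documents give none):**
- Share of recent burns in each group: 20% to 60%; Δq is the difference between groups.
- Extra natural gain in the recently burned: g = 0.3 or 0.5 SD.
- Baseline deficit in the recently burned: h, set equal to g, so they start lower and catch up.
- Baseline to follow-up correlation: 0.6.
- True campaign effect: zero.

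**Formula.** In a baseline-adjusted comparison with slope b on the baseline score:

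bias = Δq × [g − (1 − b) × h]

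With h = g this reduces to Δq × b × g. The slope is b = 0.6 / (1 + h²v), where v is the average within-group variance of the recent-burn indicator. For shares of 40% v 20%, v = (200 × 0.24 + 250 × 0.16)/450 = 0.196.

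- g = 0.3: b = 0.6/1.018 = 0.590; bias = 0.2 × 0.590 × 0.3 = 0.035 SD. Residual SD = √(1 − 0.6 × 0.590) = 0.804; SE = 0.804 × √(1/200 + 1/250) = 0.0763; bias/SE = 0.46; P(|Z + 0.46| > 1.96) = 7.5%.
- g = 0.5: b = 0.6/1.049 = 0.572; bias = 0.2 × 0.572 × 0.5 = 0.057 SD. Residual SD = 0.810; SE = 0.0769; bias/SE = 0.74; error = 11.5%.

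**Simulation of the same comparison** (2,000 data sets per setting, 200 v 250; paired entries are for g = 0.3 / g = 0.5):

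| Recent share, exposed v non-exposed | Bias (SD) | False positives, baseline score only | False positives, recent/past indicator added |
|---|---|---|---|
| 30% v 30% | 0.000 / −0.001 | 5.1% / 5.0% | 5.1% / 5.1% |
| 40% v 20% | 0.037 / 0.057 | 8.1% / 12.7% | 5.9% / 5.9% |
| 20% v 40% | −0.036 / −0.058 | 7.2% / 11.4% | 5.4% / 4.4% |
| 60% v 20% | 0.071 / 0.114 | 14.9% / 30.8% | 4.9% / 5.6% |

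The simulated rates carry a standard error of about 0.6 to 0.7 points near 8% to 12%, so they agree with the formula. With the indicator in the model, the bias was within about 0.002 SD of zero in every row.

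For Photovoice v non-exposure (50 v 250) at 40% v 20%, the bias is similar (0.034 / 0.052 SD). The smaller group gives less precision, and the false-positive rates are 5.6% / 8.3%.

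**Change within a group.** Section 4 also speaks of comparing change within groups. If 30% to 60% of a group are recently burned, natural recovery alone moves its mean by 0.3 × 0.3 = 0.09 SD to 0.6 × 0.5 = 0.30 SD. Equal shares across groups do not prevent that shift; they only cancel it in the between-group contrast.

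**The case against.** The strongest reply is that this is detail left to the analysis plan. The article defers detail to that plan, the demographic list is introduced as examples, and the baseline form in section 2.2.5 collects other variables beyond those named. Time since burn is therefore unnamed, not excluded. That stands as a limit on the wording. It does not dispose of the point: the article names a class of variables that does not include injury timing, gives that class a moderating or mediating role, and submits it to stepwise selection. A plan finished just before data lock also cannot guarantee a baseline item that was never collected.

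A second reply is that the numbers rest on assumptions. They do. The documents show no imbalance in either direction and give no recovery rate. The Introduction's remark on early limitations concerns function, not questionnaire scores, and the same section describes long-term consequences of burns.

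Three stronger readings are tempting and should be resisted.
- **All covariates are demographic.** The baseline score is usually included as well.
- **The primary results are compromised.** No passage ties time since burn to change in knowledge, attitudes or practices. The COPE Inventory too is described as measuring dispositional tendencies, which fits poorly with a recovery effect.
- **The bias is the simple product of imbalance and extra recovery.** That gives 0.2 × 0.5 = 0.10 SD and, with an unadjusted SE of √(1/200 + 1/250) = 0.095, a ratio of 1.05 and an 18% error. It leaves out the planned baseline adjustment. By the formula above, the full 0.10 SD would survive that adjustment only if recently burned survivors started level with the others (h = 0), and the documents do not say so.

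The Photovoice component is also presented as a pilot with preliminary effects, which lowers the stakes for that contrast.

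**Conclusion.** The point holds in a limited form. Recent and older burns are mixed, the groups are not described as randomised or balanced, and the model as written names no variable that separates stages of recovery. Adjustment for the baseline score reduces the resulting bias but does not remove it.

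For a 20-point imbalance in recent burns and 0.3 to 0.5 SD extra recovery, the spurious difference between 200 exposed and 250 non-exposed survivors is about 0.03 to 0.06 SD, with about 8% to 13% false positives in place of 5% (7.5% to 11.5% by formula). These figures depend on the assumed shares, recovery, equal baseline deficit and correlation of 0.6. They illustrate the mechanism and are neither a forecast nor a bound. With equal shares the between-group bias is nil; with the imbalance reversed it changes sign.

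The consequence falls mainly on the secondary psychological outcomes. This is a worthwhile, inexpensive improvement, not a flaw that invalidates the design.

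**What to change.** 1. Record time since burn on the baseline form, if it is not already recorded. This has to be settled while baseline data can still be collected.
2. In section 4, prespecify time since burn (3 months or less v longer, or log months) and its interaction with time as fixed covariates in every between-group model for survivors. Keep both outside the stepwise AIC selection.
3. Tabulate time since burn by group at baseline, so that readers can see whether an imbalance exists.
4. As a sensitivity analysis, repeat the group contrast in survivors burned more than 3 months before baseline.
5. Add burn severity in the same way only if it is recorded.

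The cost is one extra baseline item and a few degrees of freedom among 500 survivors. The sensitivity analysis will be less precise because it drops the recently burned.

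### Stepwise AIC decides which demographic covariates stay in the models of a non-randomised cohort, and the same paragraph misstates mediation, the outcome and the VIF rule

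*Protocol article*

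**What the plan says.** All the rules at issue stand in one paragraph of the Protocol article, section 4 (Data analysis plan).

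- **Main model.** Linear mixed-effects models, with the baseline measurement described as usually a covariate, time as an interacting categorical term, and a Cohen's d for Photovoice from baseline-corrected means. Significance is set by "A two-sided *p* < 0.05 indicates statistical significance".
- **Demographics.** A further step enters "demographic variables, such as age, education, gender, marital status, geographic location" and household situation. Their stated purpose is "to test for potential moderating and mediating effects on behavioural intention related to burn prevention and first-aid practices".
- **Selection.** "A stepwise selection of the variables will be conducted to determine which variables to keep in the model". The criterion is that "we will immediately eliminate those that do not reduce the Akaike information criterion (AIC"), using stepAIC.
- **Collinearity.** "a variance inflation estimate of less than 5 will be used to determine whether collinearity is present".

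The design sections supply the context. Section 2.1 describes a cohort with an exposure group (200 survivors and 100 caregivers), a non-exposure group (250 survivors) and a Photovoice group (50 survivors). Section 2.2.1 recruits by snowball and purposive sampling. Section 2.2.4.1 makes Photovoice entry depend on willingness and availability. The Abstract says that the design evaluates the impact of the campaign and any added effect of Photovoice.

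**The concern.** Campaign impact and added Photovoice effect are between-group claims. Without randomisation, age, education, gender, residence and similar variables may differ between the groups and also predict the outcomes. AIC retains a variable for improving the prediction of the outcome and takes no account of how unequal the groups are on it. A variable with a modest effect on the outcome but a large imbalance is therefore easily dropped, and the group estimate then carries its bias. Each outcome may also end up with a different covariate set.

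Three statements in the paragraph are wrong however the selection rule is read:

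- Age and gender cannot be altered by a campaign, and education or residence recorded at baseline precede it. They can moderate an effect but cannot mediate it.
- Behavioural intention is the stated dependent variable, but nothing in Table 1 or in the measures of section 2.2.5 is said to capture it.
- A low variance inflation factor is a sign that collinearity is absent.

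**Working it through.** The plan gives no operating figure for the selection rule, and its sample size does not depend on the rule, so there is no stated number to reproduce.

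**1. What the AIC rule means for one term.** Adding one parameter changes AIC by 2 − LR, where LR is the likelihood-ratio chi-square on 1 df. The term stays if LR > 2, and P(χ²₁ > 2) = 0.157.

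- Six independent pure-noise terms (six demographics are named): P(at least one kept) = 1 − (1 − 0.157)⁶ = 0.64.
- A noise term that has been kept then shows p < 0.05 with probability 0.05 / 0.157 = 0.32. A p-value read after selection does not have its nominal meaning.

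**2. Effect on a group comparison, if the rule governs it.** Group sizes come from section 2.1. Everything else is assumed, because the documents give neither imbalances nor covariate effects.

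- Six independent covariates, all shifted between groups by the same amount (0 to 0.5 SD), each with the same effect on the outcome (0 to 0.10 SD), and no true group effect.
- A linear model at one follow-up, with group and baseline score always included.
- Bidirectional stepwise AIC over the six covariates, 1,500 replicates per setting. The Monte Carlo standard error at 5% is √(0.05 × 0.95 / 1500) = 0.006.

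Selected rejection rates at two-sided 0.05:

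| Groups | Imbalance (SD) | Covariate effect (SD) | Fixed set | Stepwise AIC | No covariates | Share of covariates kept |
|---|---|---|---|---|---|---|
| 200 v 250 | 0 | 0.05 | 0.047 | 0.051 | 0.045 | 43% |
| 200 v 250 | 0.2 | 0.05 | 0.069 | 0.076 | 0.109 | 43% |
| 200 v 250 | 0.3 | 0.05 | 0.050 | 0.071 | 0.175 | 43% |
| 200 v 250 | 0.5 | 0.05 | 0.051 | 0.111 | 0.419 | 42% |
| 200 v 250 | 0.5 | 0.10 | 0.049 | 0.084 | 0.947 | 84% |
| 50 v 250 | 0 | 0.05 | 0.050 | 0.058 | 0.053 | 34% |
| 50 v 250 | 0.2 | 0.05 | 0.051 | 0.061 | 0.073 | 35% |
| 50 v 250 | 0.3 | 0.05 | 0.051 | 0.061 | 0.104 | 35% |
| 50 v 250 | 0.5 | 0.05 | 0.054 | 0.087 | 0.195 | 35% |

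Over all 24 settings, stepwise gave 0.046 to 0.111 and the fixed set 0.042 to 0.069. The fixed-set test is exact in this model, so 0.069 is simulation noise. That row is best read as stepwise against fixed set, 0.076 against 0.069.

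A second set of runs (3,000 replicates, forward AIC) used 160 v 200, which is 200 and 250 survivors less 20% dropout. It gave 4.8–5.8% at an imbalance of 0.1 SD, 5.3–6.3% at 0.2 SD and 6.2–7.6% at 0.3 SD. With covariate effects of mixed sign at 0.3 SD it gave 6.4–6.8%. Full adjustment gave 4.2–5.6% throughout.

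**3. The VIF rule.** VIF = 1 / (1 − R²). Uncorrelated predictors have R² = 0 and VIF = 1. VIF = 5 corresponds to R² = 1 − 1/5 = 0.80. As written, the rule declares uncorrelated predictors collinear and passes those with R² above 0.80.

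**4. The outcome.** Table 1 lists KAP, the nine psychological scales, photo reflection and campaign effectiveness. The sample practice item of the KAP (section 2.2.5.1) asks whether the respondent has ever taken a first-aid step. That is past behaviour, not intention.

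**The case against.** The strongest reply is that the stepwise rule is not stated to govern the campaign comparison. It follows a sentence that opens an additional step, in which the demographics "will be included in the linear mixed models to test for potential moderating and mediating effects on behavioural intention". They are nowhere called confounders. The paragraph also begins by wording the aim as change within groups, where a fixed characteristic cancels from a person's own change. This stands in part: control of the group estimate by stepAIC is a fair reading of 'the model', not an explicit statement. However, the Abstract and the Photovoice effect size call for between-group estimates, and apart from the baseline score this is the only covariate rule given.

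The second reply is that the harm is small and assumed. That also stands. The excess is typically one to two percentage points, and it nearly vanishes when the groups are balanced.

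Third, the VIF sentence is probably a slip. It still needs correcting, because it would be applied as written.

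A reader might also infer that clustering by the 12 centres is ignored, from "This method considers correlations within participants, allowing them to be modelled appropriately". The text does not support that. The model is said to have fixed and random effects, participant is not named as the only random effect, and a centre term is a detail that an article may leave to the analysis plan it announces.

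**Conclusion.** The point holds. The article states these rules down to the R function, so it is not a matter of detail left to a later plan.

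- **Selection rule.** If it governs the group estimates, type I error is about 5% to 8% in most of the settings tried and 11% in the worst (200 v 250, 0.5 SD imbalance, 0.05 SD effects), against about 5% with a fixed set. These figures rest on assumed imbalances and effects and on a simplified single-follow-up model. If it governs only the moderator model, the p-values of the selected terms are still unreliable.
- **Mediation, outcome and VIF wording.** These are errors of statement and need no assumption.

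Two stronger readings should be resisted. One is that the campaign p-values as a whole are invalid: neither the text nor the size of the inflation supports that. The other is that the confidence interval is too narrow: the runs measured rejection rates, which mix bias with interval width, so interval width was not assessed.

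**What to change.** 1. For every between-group estimate, prespecify one adjustment set and keep it regardless of AIC: baseline score (always, not usually), age, gender, education, marital status, rural or urban residence, and household situation. The plan already names all of these, and the set applies to survivors and caregivers alike. Confirm that household situation is on the demographic questionnaire; section 2.2.5 does not list it by name but leaves room for other variables.
2. Confine stepAIC to analyses labelled exploratory.
3. Test moderation through group × covariate terms, also labelled exploratory.
4. Delete 'mediating' where it refers to demographics.
5. Either define a measure of behavioural intention or name a measured outcome in its place. Substituting the KAP practice score without comment would change the construct.
6. Reword the collinearity rule so that a VIF of 5 or more indicates collinearity.

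The cost is redrafting and a few degrees of freedom, out of about 360 evaluable survivors (450 × 0.8). The adjustment set needs no new data if the household item is already on the form.
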